## Statistical Considerations and Analysis

### Study Hypothesis

This study is designed to demonstrate that carbon ion therapy can significantly improve LPFS compared with proton therapy in the treatment of skull base chordomas. Primary objective is the comparison of the two treatment groups.

Null hypothesis H_0_: The survival functions of LPFS of the two therapies are equal, hazard ratio = 1.

Alternative hypothesis H_1_: The survival functions of LPFS of the two therapies are not equal, hazard ratio ≠ 1.

### Sample Size Determination

The sample size is calculated on the basis of the following assumptions:

• LPFS rate 5 years after radiation therapy of 70% 1) for proton therapy, hazard λ_1 _= 0.0713, and 80% for carbon ion therapy, hazard λ_2 _= 0.0446 (hazard ratio = 1.599).

• Recruitment period of 5 years, with constant accrual rate of 20% patients per year and a follow-up time of 8 years.

• One interim analysis according to a group sequential design with two stages.

Formula of Schoenfeld [20,21] used for the calculation of the number of accumulated events. For a two-sided logrank test with an overall two-sided significance level of 0.05 (including interim and final analyses) and power of 0.80, 143 events are required. The critical values and the test characteristics of the group sequential test design were calculated for an O'Brien and Fleming type alpha spending function. The computation assumes equal allocation to the two groups (n_2_/n_1 _= 1). Assuming an accrual time of 5 and a maximum observation time of 13 years a total of 319 patients is expected to yield the necessary number of events if the accrual rate is constant. Under these assumptions, the time point of the interim analysis should be 7 years after the first patient is entered. The ADDPLAN, Version 4.0 calculator was used for the sample size estimation. With the assumption that approximately 7% of the patients will be lost to follow-up a total of 344 patients will be needed to accumulate 143 events.

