## Organization, Workflow and Follow-up

Patient data will be collected and documented pseudonymously using electronic data processing (e.g. patient initials, date of birth and study number) at the study office at HIT. Table 3 presents a brief workflow.

**Table 3 T3:** Workflow time table

Approval of ethics committee
↓
Diagnosis of chordoma of the skull base and completion of pre-radiation treatment examinations (biopsy, operation, staging)
↓
Informed consent of the patient and patient registration by the study office at HIT
↓
Stratification and Randomisation
↓
Arm A: carbon ion RT (63 Gy E ± 5%, fractionation 4-6 × 3.0 Gy E) Arm B: proton RT (72 Gy E ± 5%, fractionation 4-6 × 2.0 Gy E)
↓
Treatment planning for particle therapy
↓
Particle therapy
↓
Follow-up

After randomisation the study number will be assigned.

The following study data will be collected at the study office at HIT:

1. Medical reports including pathology reports and results of staging and additional pre-treatment examinations

2. Documentation of RT (dose distributions and DVH) and position checks

3. Prescribed total target dose and fraction doses, treatment interruptions >4 days

4. Toxicity data

5. Follow-up forms

6. Trial-related documentation including severe AE (CTCAE Grad ≥ 3) will be reported immediately to the study office and the principal investigator of the study

7. The date of local recurrence (MRT or CT - morphological tumour progress in the former irradiated region), distant metastases or death of the patient will be reported and documented.

Local recurrences will be confirmed radiologically and histologically whenever possible. At least two medical doctors (radiation oncologist and/or radiologist) will be required to judge of the recurrence or toxicity.

Every patient is followed for LPFS and trial-related AEs for a time period of 8 years. Furthermore, patients will be followed for survival and locoregional recurrences for a time period of 8 years after completion of the irradiation.

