The first and the second follow-up examination will be performed 4-6 weeks and 3 months after completion of RT (follow-up 1 and 2). Follow-up examinations will then be scheduled after 6 months (follow-up 3), 9-12 months (follow-up 4), and then once a year for further 6 years (follow-up 5, 6 and 7). Additional visits will be scheduled as necessary. Acute toxicity is assessed at least weekly during RT and documented at the end of the RT series, 6 weeks after completion of RT and 3 months after RT. Late toxicity will be documented in regular intervals of 6 or 12 months during the observation period. All the patients will be observed for radiation specific acute and late AEs for the time of at least 8 years after irradiation. The maximum grade of toxicity will be determined for each patient.

The Common Terminology Criteria for Adverse Events V4.0 (CTCAE V.4.0) will be used to grade acute toxicity from radiation therapy. The criteria are relevant from the 8th irradiation day until day 90, i.e. until the 1st follow-up visit. Thereafter, the RTOG/EORTC Criteria of Late Effects will be utilized. All acute radiation effects will be documented on an Acute Radiation Effect-Form. In addition, the AE-Form and/or SAE-Form will be filled out. RTOG/EORTC Late Morbidity Scoring Scheme will be used to grade toxicity from radiation therapy occurring later than 90 days after its start, i.e. beyond the 1st follow-up visit. All late radiation effects will be documented on a Late Radiation Effect-Form. In addition, an AE-Form and/or SAE-Form will be filled out, if late radiation effects appear.

The follow-up examinations contain:

- Medical history

- Clinical examination

- MRI or CT of the head

- Documentation of acute side effects/AE (CTCAE V.4.0) up to 90 days after RT

- Documentation of late side effects/AE (RTOG/EORTC) after 90 days after RT

- Reporting/documentation of acute grade 3 or 4 toxicity or grade 3, 4 or 5 late effects.

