### Study duration and interruption criteria

Accrual period for the trial will be approximately 5 years starting on autumn 2010. The study ends with the enrollment of planned 344 patients. Our study design contains interim analysis after observation period of 7 years. Definite assessments of LPFS, survival and for radiation specific AEs will be possible approximately 8 years after completion of radiation therapy of the last recruited patient.

The individual reasons for the study interruption are the patient dead or the withdrawing agreement of the patient to participate in the study.

With proven recurrence of disease or the development of distant metastases, the patient will be censored for our study and will be eligible for any additional appropriate therapy or inclusion in other investigative protocols, but should still be followed in order to document survival and radiation specific AEs.

The study can be early terminated under following considerations:

- high incidence of unknown AEs or increase in known AEs with the disadvantageous proportion between risk and benefits of the proposed radiation therapy;

- unacceptable high rates of SAEs;

- other reasons challenging the ethical basis;

- official decision.

All subjects who have adverse events, whether considered associated with the therapy, must be monitored to determine the outcome. The clinical course of the adverse event will be followed up according to accepted standards of medical practice, even after the end of the period of observation, until a satisfactory explanation is found or the investigator considers it medically justifiable to terminate follow-up. Should the adverse event result in death, a full pathologist's report should be supplied, if possible.

Each adverse event occurring in connection with the therapy has to be documented, independent of the cause.

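### The 319/344 patients yield 143 events and 80% power only if everyone is observed to a common 13-year cut-off, but the written LPFS follow-up is 8 years per patient

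*Protocol article*

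**What the plan says.** All places are in the protocol article.

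- **Sample Size Determination.** Five-year LPFS is taken as 70% for protons and 80% for carbon ions, with constant hazards: "for proton therapy, hazard λ_1 _= 0.0713" and "80% for carbon ion therapy, hazard λ_2 _= 0.0446 (hazard ratio = 1.599". Accrual is uniform over 5 years and the follow-up time is given as 8 years. The event target is stated as "power of 0.80, 143 events are required". The patient number follows: "Assuming an accrual time of 5 and a maximum observation time of 13 years a total of 319 patients is expected" to produce those events. Allowing for 7% loss raises it to 344.
- **Organization, Workflow and Follow-up.** "Every patient is followed for LPFS and trial-related AEs for a time period of 8 years". The next sentence gives 8 years after irradiation for survival and locoregional recurrence. Visits run to 9-12 months after radiotherapy "and then once a year for further 6 years (follow-up 5, 6 and 7", that is, to about year 7. Each follow-up examination includes MRI or CT of the head.
- **Study duration and interruption criteria.** The definitive LPFS assessment is placed about 8 years after the last recruited patient finishes radiotherapy.
- **Primary efficacy analysis.** Patients with neither local progression nor death on study are censored at their last tumour assessment.

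**The concern.** Two durations in the current text do not fit together. A maximum observation of 13 years with 5 years of accrual means that the first patient is observed for 13 years and the last for 8. A follow-up of 8 years for every patient means that nobody is observed for longer than 8.

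The difference matters because the hazards are low: a good share of the 143 expected events falls in years 8 to 13 of the early entrants. If their LPFS follow-up stops at year 8, those events are not collected. Postponing the analysis cannot recover them, because each patient's own observation has ended. The primary comparison would then have less power than stated, in a rare disease where the trial would be hard to repeat.

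**Working it through.** **Inputs** (all from Sample Size Determination): 5-year LPFS 70% and 80%; two-sided alpha 0.05; power 0.80; 1:1 allocation; uniform accrual over A = 5 years; total duration T = 13 years; loss 7%.

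**1. Hazards.** λ1 = -ln(0.70)/5 = 0.0713; λ2 = -ln(0.80)/5 = 0.0446; ratio 1.598 unrounded (the plan's 1.599 comes from the rounded hazards). ln(1.598) = 0.469.

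**2. Events (Schoenfeld).** 4 × (1.960 + 0.842)² / 0.469² = 142.7, so 143. The plan's figure reproduces. With the two-stage boundaries (2.9626 at the interim, 1.9686 at the end), power at 143 events is 0.799.

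**3. Patients with a common cut-off at 13 years.** Event probability per arm = 1 - [exp(-8λ) - exp(-13λ)]/(5λ).
- Protons 0.525; carbon ions 0.373; mean 0.4487.
- 143/0.4487 = 318.7, so 319. The plan's figure reproduces.
- 319/0.93 = 343.01, so 344. The plan's figure reproduces.

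**4. Patients with 8 years each.** Event probability per arm = 1 - exp(-8λ).
- Protons 0.435; carbon ions 0.300; mean 0.3676.
- 319 × 0.3676 = 117 events; 344 × 0.3676 = 126 events.
- Needed for 143: 143/0.3676 = 389.06, so 390 evaluable patients (390/0.93, so 420 after 7% loss).

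**5. Power.** Φ(√d × 0.469/2 - 1.96) for d events.

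| LPFS observation | Mean event probability | Events, 319 evaluable | Power | Events, all 344, no loss | Power |
|---|---|---|---|---|---|
| Common cut-off at 13 years | 0.449 | 143 | 80% | 154 | not needed here |
| 8 years per patient | 0.368 | 117 | 72% | 126 | 75% |
| 7 years per patient | 0.331 | 105 | 67% | 114 | 71% |

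The two-stage boundaries change these powers by less than half a percentage point.

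**6. Sensitivity to the starting point.** If the 8 years run from the end of radiotherapy, I assume 8.1 to 8.25 years from randomisation. Then 319 patients give 118 to 120 events and power of 72-73%. The conclusion is unchanged.

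**7. The 7-year row is a lower bound.** It treats all observation as ending with the last scheduled scan. Death from any cause is an LPFS event, and survival is followed to 8 years after irradiation, so deaths after the last scan still count.

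**8. Interim.** At 7 years after first entry, 319 patients give 71.9 events, against 71.5 for half of 143. No patient has reached year 8 by then, so the timing is unaffected. The information fraction is not: 71.5/117 = 61% and 71.5/126 = 57%, in place of 50%.

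**The case against.** The strongest reply is that 8 years was meant as a minimum. The sample size section uses 8 years for the time after accrual closes (5 + 8 = 13). The definitive LPFS assessment is set about 8 years after the last patient's radiotherapy, which matches a common cut-off. The individual reasons listed for leaving the study are death and withdrawal, not reaching year 8, and additional visits are allowed. This reading is possible, and for that reason the loss of power is conditional. But the only wording that makes 8 years a minimum concerns adverse events. The LPFS sentence has no such qualifier, the assessment time says when analysis becomes possible and not that early entrants stay under imaging, and the visit plan stops sooner still. Nor is this an effect of condensing a protocol into an article, because both durations are printed.

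A reader might also draw stronger conclusions that the document does not support:

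- *Imaging stops at year 4 because only visits 5, 6 and 7 are named.* The same sentence says yearly for six more years; the parenthesis looks like a numbering slip.
- *Every event after the last scan is lost.* Only patients who neither progress nor die on study are censored at the last assessment.
- *The final analysis waits for 143 events that never come.* Only the interim is triggered by events; the final assessment has a calendar point.
- *The interim's type I error is broken.* The Interim Analysis section sets the boundary by the current information time through a spending function, and the study continues whatever the result.
- *Event collection ends at recruitment, because* "The study ends with the enrollment of planned 344 patients". The same section places the definitive LPFS assessment years later, so this is loose wording for the end of recruitment.

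**Conclusion.** The point holds in conditional form. The arithmetic for 143, 319 and 344 is correct, but it rests on a common cut-off 13 years after first entry that the follow-up section does not provide. If LPFS follow-up is 8 years per patient, as written, expected events fall by 17 to 26 (to about 126 or 117) and power falls from 80% to about 75% or 72%. If tumour assessment ends with the visit plan at about year 7, 319 patients give at least about 105 events (67%).

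These figures assume the plan's constant hazards and uniform accrual. The lower value in each pair takes 319 evaluable patients after 7% loss; the upper takes all 344 with no loss. If the sponsor intended 8 years as a minimum, the stated power stands, but the follow-up text and visit plan still have to say so, because they decide what is collected.

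**What to change.** Reconcile Sample Size Determination with Organization, Workflow and Follow-up, in one of two ways.

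1. **Keep the 13-year basis.** State that LPFS follow-up, with the scheduled imaging, continues for every patient until one common cut-off about 8 years after the last patient. Extend the visit list to match, and correct its numbering. With uniform accrual over 5 years, the extra follow-up beyond year 8 runs from 0 to 5 years, or about 2.5 more annual visits per patient on average. Counted from the present end of the visit plan at about year 7, it is one more each, about 3.5. The patient number and the stated power do not change.
2. **Keep 8 years per patient.** Restate expected events as about 117-126 and power as about 72-75%, and base the interim's 50% point on that number. Extend the visit list to year 8. The cost is a lower stated power. Restoring 80% would take about 390 evaluable patients, or 420 with 7% loss.

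The first option works only if it is in force before the first entrants reach the end of their written follow-up. In either case, reword the sentence on the study ending so that it refers to recruitment.

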### Analysis Populations and General Considerations

Analysis populations will be defined as follows:

The ITT population will include all patients who are randomised, with radiation therapy administration designated according to initial randomisation, regardless of whether patients receive study treatment or receive a different treatment from that to which they were randomised. This will be the primary population for evaluating all efficacy endpoints as well as subject characteristics.

The safety population consists of all subjects who received at least one dose of irradiation administration designated according to actual study treatment received.

The PP population will consist of all subjects of the ITT population who completed the particle therapy, have at least 2 post-baseline assessments regarding the primary endpoint without pre-specified (in the statistical analysis plan), selected major protocol deviations thought to impact on efficacy analysis.

The statistical analysis will be done as soon as the database has been declared to be complete and accurate and has been locked. The details of the analysis will be laid out in the statistical analysis plan, which will be finalized and approved prior to the database lock. It has to be authorized before by the biometrician and the principle investigator. Missing values will not be replaced or imputed. For patients with incomplete follow-up, time to last follow-up date will be used as the censoring time in the analysis of time-to-event data.

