### Carbon ion/Proton RT

Carbon ion RT planning is performed using the treatment planning software including biological plan optimization for carbon ions. Two to maximum four irradiation fields will be chosen. At HIT the intensity-controlled raster-scan system will be used for beam application. Considering the tolerance dose to organs at risk a dose of 63 Gy E ± 5% in 20-22 fractions for carbon ions and 72 Gy E ± 5% in 34-37 fractions for protons for chordoma patients will be prescribed to the maximum of the calculated dose distribution for the target volume (PTV1). Treatment planning aims at coverage of the PTV1 and PTV2 with the 95%-isodose line of the prescribed dose.

For carbon ion therapy dose specification is based on biologic equivalent dose because of the higher relative biologic effectiveness (RBE) of carbon ions, which differs throughout the target volume due to its dependence on various factors. RBE will be calculated for each voxel throughout the target volumes and biological optimization will be performed. The dose prescription used is related to the isoeffective dose Gy E using daily fractions of 3 Gy E and a weekly fractionation of 4-6 × 3 Gy E.

For proton therapy RBE of 1.1 will be used using daily fractions of 2 Gy E and a weekly fractionation of 4-6 × 2 Gy E.

Evaluation of DVH for the dose distribution will be performed with regards to assess plan quality. Maximum chiasm dose, maximum right and left optic nerves dose, maximum brain steam dose, median brain steam dose, maximum dose to spinal cord, median dose to spinal cord will be reported.

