### Efficacy Analysis

#### Primary efficacy analysis

LPFS is defined as the time from date of randomisation to local recurrence or death from any cause in the absence of documented local disease progression. LPFS will be censored on the date of the last tumour assessment on study for patients who do not have local tumour progression and who do not die while on study.

A log-rank test (two-sided) will be used to compare LPFS between the two treatments. The LPFS-rates will be derived from the Kaplan Meier estimate [22] and the confidence intervals will be calculated using Greenwood's formula.

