#### Secondary efficacy analyses

A sensitivity analysis will be performed on the primary efficacy endpoint to assess the impact of protocol deviations using the per protocol analysis set.

A hazard ratio with 95% confidence interval for the experimental arm relative to control arm will be estimated by proportional hazard regression [23-25] with treatment, gender, age (< 30, ≥ 30 years), tumour size (< 70 ml, ≥ 70 ml), compression of OAR (yes/no) as covariates. A logistic regression analysis [26] will be carried out to identify relevant prognostic factors. Benefit from intervention (yes or no) will be defined as belonging to the patients groups (low-risk, high-risk group) which lay above the 50% percentile of LPFS.

The analyses of OS, PFS and metastasis free survival will be conducted using log-rank test. The Kaplan-Meier method will be used to obtain the estimates of the survival functions and the 95% confidence intervals will be estimated using Greenwood's formula. Covariates will not be included in the calculation.

All of these secondary analyses will be conducted at the 0.05 level of significance.

Descriptive statistics will be provided for all other secondary endpoints. Additional exploratory analyses will be used as appropriate. Generally, results will be given by summaries of the data as indicated above together with the test statistics and their associated p-values. Appropriate confidence intervals of estimates of effect will be given to quantify the degree of uncertainty of the point estimates.

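### The per-protocol set requires two post-baseline assessments even of patients who have already had an LPFS event, so early failures are excluded because of their outcome (minor; sensitivity analysis only)

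*Protocol article*

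**What the plan says.** Under Analysis Populations and General Considerations, the per-protocol set consists of ITT patients who "completed the particle therapy, have at least 2 post-baseline assessments regarding the primary endpoint" and have none of the major deviations to be listed in the statistical analysis plan. That list is left to the plan; the two-assessment condition is fixed in the article. The same section says of the ITT population: "This will be the primary population for evaluating all efficacy endpoints as well as subject characteristics".

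Secondary efficacy analyses gives the set its use: "A sensitivity analysis will be performed on the primary efficacy endpoint to assess the impact of protocol deviations using the per protocol analysis set".

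Three other places determine how the condition works:
- **Endpoint** (Primary efficacy analysis): "LPFS is defined as the time from date of randomisation to local recurrence or death from any cause". Death is an event, and the clock starts at randomisation.
- **Visits** (Organization, Workflow and Follow-up): "The first and the second follow-up examination will be performed 4-6 weeks and 3 months after completion of RT". The examinations include "MRI or CT of the head".
- **After recurrence or metastasis** (Study duration and interruption criteria): the patient "should still be followed in order to document survival and radiation specific AEs". Further tumour assessment is not mentioned there.

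**The concern.** A per-protocol set should depend on adherence: eligibility, treatment received, and deviations judged without regard to outcome. Here membership also depends on remaining under assessment until about three months after radiotherapy. A patient who dies before then has a complete primary-endpoint record and no deviation, yet cannot qualify. The same is true of a patient whose recurrence is found at the first visit and who is not assessed again.

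If the per-protocol and ITT results differed, a reader could not tell how much was due to deviations and how much to deleted early events. Patients who are kept also contribute time from randomisation during which, for most of them, an event would have removed them from the set. The gap matters most if the two beams differ in early failures, because those are the events the rule deletes.

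**Working it through.** **The plan's own figures.** From Sample Size Determination, λ₁ = −ln(0.70)/5 = 0.0713 and λ₂ = −ln(0.80)/5 = 0.0446 per year; the ratio is 1.598 (stated as 1.599). Schoenfeld: 4 × (1.960 + 0.842)² / (ln 1.598)² = 142.7, so 143 events. Uniform accrual over 5 years with analysis at 13 years gives 318.7, so 319 patients; 319/0.93 = 343.01, so 344. All three stated figures are reproduced and none is disputed.

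**Time to the second visit.** Carbon ion/Proton RT gives "63 Gy E ± 5% in 20-22 fractions for carbon ions and 72 Gy E ± 5% in 34-37 fractions for protons", at 4 to 6 fractions a week. Assumed here: 4.2 weeks (carbon) and 7.2 weeks (proton), which is 21 and 36 fractions at five a week, and 13 weeks for three months. The interval from randomisation to the start of radiotherapy is not stated and is set to zero at first.
- Carbon: (4.2 + 13)/52 = 0.33 years
- Proton: (7.2 + 13)/52 = 0.39 years

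**Events before the second visit**, 172 per arm:
- Proton: 1 − exp(−0.0713 × 0.39) = 2.7%, or 4.7 events
- Carbon: 1 − exp(−0.0446 × 0.33) = 1.5%, or 2.5 events
- Total: 7.2

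**Events that the completion condition already removes** (during radiotherapy):
- Proton: 172 × [1 − exp(−0.0713 × 7.2/52)] = 1.7
- Carbon: 172 × [1 − exp(−0.0446 × 4.2/52)] = 0.6
- Total: 2.3

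**Left to the assessment condition:** 7.2 − 2.3 = 4.9 events, or 4.9/143 = 3.4%. A delay before radiotherapy does not raise this. Patients with an event during the delay do not complete therapy either, so only the 13 weeks after radiotherapy count. At most, 172 × [1 − exp(−0.0713 × 0.25)] + 172 × [1 − exp(−0.0446 × 0.25)] = 3.0 + 1.9 = 4.9.

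**If it mainly catches deaths.** The Background reports carbon-series survival of 91.8% at 3 years and 88.5% at 5 years. With a constant hazard, the same in both arms, these give −ln(0.918)/3 = 0.0285 and −ln(0.885)/5 = 0.0244 per year. Over 13 weeks, 344 × [1 − exp(−0.0285 × 0.25)] = 2.4 and 344 × [1 − exp(−0.0244 × 0.25)] = 2.1.

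**Effect on the LPFS rate.** Removing all events in a 13-week window multiplies five-year LPFS by at most exp(λ × 0.25): 0.70 × 1.018 = 71.3% for protons and 0.80 × 1.011 = 80.9% for carbon. With every event before 0.33 to 0.50 years from randomisation removed, so that the completion condition is included, the figures are 71.7–72.5% and 81.2–81.8%.

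**Effect on the hazard ratio (carbon/proton).** The design value is 1/1.598 = 0.626. Simulation at the planned hazards with 319 patients, a rate-ratio estimator and all events before 0.5 years removed gives 0.622 (ITT) and 0.626 (per protocol). A Cox simulation with 172 per arm and the arm-specific windows above gives 0.631 and 0.634; the standard error of the log hazard ratio is about 0.17.

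**If early events differ by arm.** This is an illustration with an assumed 5% of extra events within 0.5 years in one arm (rate-ratio estimator). It removes all events before 0.5 years, so it overstates what the assessment condition does alone.

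| Extra early events | ITT | Per protocol |
|---|---|---|
| None | 0.62 | 0.63 |
| 5% on carbon | 0.71 | 0.63 |
| 5% on proton | 0.56 | 0.63 |

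**Window by arm.** Visits are timed from the end of radiotherapy. Counted from randomisation, the period in which an event can exclude a patient is longer on protons by 7.2 − 4.2 = 3 weeks. At equal weekly rates the range is 34/6 − 20/6 = 2.3 weeks to 37/4 − 22/4 = 3.75 weeks.

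**The case against.** The strongest objection concerns direction. More early events are removed from the proton arm, so a reader might infer that the rule pulls the per-protocol hazard ratio materially towards 1. It does not. The log-rank test and Cox regression use only the risk sets at event times. Patients with early events are in no later risk set, so deleting them leaves the later comparison intact. Under proportional hazards the rule acts like a landmark, and the simulated shift is far below the standard error. This stands.

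A second tempting reading is that all 7 or so events before the three-month visit are lost to this condition. Several points count against that, and they stand too:
- Events during radiotherapy mostly fail the completion condition anyway.
- A recurrence first seen at the second visit comes with two assessments and stays in.
- The article does not say that tumour follow-up stops after recurrence. Organization, Workflow and Follow-up continues follow-up for locoregional recurrence for 8 years, asks for radiological and histological confirmation where possible, and allows additional visits. A patient whose recurrence is found at the first visit may therefore still qualify.

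It can also be said that the article does not define what counts as an assessment of the primary endpoint, so a recorded death might count as one, and that details are left to a statistical analysis plan not shown. This makes the size uncertain but does not remove the point. The minimum of two is fixed in the article without an exception for events, and a patient who dies before the first visit would still have only one assessment even if the death counted.

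Finally, it would be too strong to call the per-protocol result uninterpretable. A loss of a few events with an almost unchanged hazard ratio does not support that.

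**Conclusion.** The point holds, with minor severity. The two-assessment condition excludes some patients because of their outcome, in an analysis meant to isolate protocol deviations. At the planned hazards it removes at most about 5 of 143 events beyond the completion condition, and possibly only 2 to 3. Five-year per-protocol LPFS rises by about 1 percentage point in each arm, and the hazard ratio is almost unchanged under proportional hazards.

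The practical weakness is that the analysis would conceal an early difference between arms if there were one. The documents give no evidence that there will be, and the 5% used above is an assumption. The counts rest on constant hazards from randomisation, 344 patients, the assumed radiotherapy durations and, for the lower figure, carbon-series survival applied to both arms. The ITT primary analysis, the 143 events and the sample size are not touched.

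**What to change.** Add one sentence to the per-protocol definition: a patient with an LPFS event at any time meets the assessment requirement. The minimum of two then applies only to patients without an event. Alternatively, drop the minimum. Either way, the assessment minimum no longer excludes anyone for having had an event, and for patients with an event the set rests on eligibility, completion of the allocated particle therapy and the pre-specified major deviations. The completion condition will still exclude patients who fail during treatment, which should be stated when the result is reported.

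The cost is one sentence in the protocol, carried into the statistical analysis plan. It needs no extra patients or visits and does not affect the significance level or the power of the primary analysis.
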